## Abstract

**Background:**

Severe mental illnesses like schizophrenia and bipolar disorder are known to be diseases that to some extent, but not entirely can be understood genetically. The dominating hypothesis is that these disorders should be understood in a neurodevelopmental perspective where genes and environment as well as gene-environment-interactions contribute to the risk of developing the disease. We aim to analyse the influences of genetic risk and environmental factors in a population of 520 7-year-old children with either 0, 1 or 2 parents diagnosed with schizophrenia spectrum psychosis or bipolar disorder on mental health and level of functioning. We hypothesize that a larger proportion of children growing up with an ill parent will display abnormal or delayed development, behavioural problems or psychiatric symptoms compared to the healthy controls.

**Methods/design:**

We are establishing a cohort of 520 7-year-old children and both their parents for a comprehensive investigation with main outcome measures being neurocognition, behaviour, psychopathology and neuromotor development of the child. Parents and children are examined with a comprehensive battery of instruments and are asked for genetic material (saliva or blood) for genetic analyses. The participants are recruited via Danish registers to ensure representativity. Data from registers concerning social status, birth complications, somatic illnesses and hospitalization are included in the database. Psychological and relational factors like emotional climate in the family, degree of stimulation and support in the home and attachment style are also investigated.

**Discussion:**

Data collection started January 1, 2013, and is successfully ongoing. By Aug 2015 424 families are included. About 20 % of the invited families decline to participate, equal for all groups.

## Introduction

Schizophrenia and bipolar disorder are among the most severe and disabling mental disorders, influencing both patients, relatives and society [1]. Our knowledge about the etiology and development of these diseases is still limited and therefore prevention strategies are not specific or proven effective.

It has recently been shown that mental diseases like schizophrenia, major depression and bipolar disorder may be quite closely related genetically, meaning that there is a considerable genetic overlap between the three different diagnoses [2]. Based on this recent meta-analysis it was found that offspring of parents with one of the mentioned diseases not only had an increased risk of developing the same illness as their ill parent, but also an increased risk of developing the other two disorders.

*Schizophrenia* is known as a severe and complex mental disorder, most likely caused by several interacting genetic and environmental factors, each having only a limited effect and predictive value. The dominating hypothesis is that schizophrenia is a neurodevelopmental disorder [3]. The genetic contribution to the etiology of schizophrenia is among the best investigated in psychiatry and is well-documented in family, twin and adoption studies as well as in GWAS studies [4]. Also, studies have shown that genetic risk factors and environmental factors may interact with and be influenced by each other and thus also influence the risk of developing psychosis or bipolar disorder [5].

Children born to parents with *bipolar disorder* also have an increased risk of developing other mental disorders and specifically early-onset bipolar spectrum disorders [6, 7]. Most adults with bipolar disorder experience their first mood symptoms before the age of 21 years, whereas most children at high genetic risk who develop bipolar disorder later in life show manifest symptoms of the disorder much earlier, often before the age of 12 years.

### Objectives

The aims of the Danish High Risk and Resilience Study-VIA 7 are:to analyse the influences of familial risk and environmental factors, including rearing conditions in childhood among a population of 7-year-old children with either 0, 1 or 2 parents diagnosed with schizophrenia spectrum psychosis or bipolar disorder, especially focusing on psychopathology, cognition, neuromotor, and psychosocial development;to identify early risk markers of schizophrenia and bipolar disorder to establish a basis for future primary preventive interventions in the premorbid phase;to get an overview of the kind and the intensity of help and support that the families have received from the community from the time when the child was born until the age of 7.

## Background

### Optimal designs for investigating gene-environment interactions

#### The high risk approach

Theoretically, optimal designs for investigating interaction between environmental and genetic risk factors in childhood and adolescence with respect to development of schizophrenia or bipolar disorder, would be randomized clinical studies with the individuals being exposed to poor environmental conditions, or adoption or twin studies. However, randomized clinical studies are not ethically acceptable and adoption studies with monozygote twins growing up under different conditions, are very rare.

Early signs of psychopathology and development of schizophrenia or bipolar disorder are rarely found in the general population, which makes studies of populations with an increased risk profile (‘high risk studies’) highly relevant for investigating the development of these disorders and the influence of genetic risk. One of the most famous studies in the field of schizophrenia research is ‘The Copenhagen High Risk Project’ [8], which so far is one of the largest studies, covering 207 children of mothers diagnosed with schizophrenia. It was started in 1962, when the children were on average 15 years old, and the study has contributed to our current knowledge with considerable and important results. One of its major contributions was to show that schizophrenia was at least partly familial. It was also one of the first studies to show the specific impairments in these children at high risk in domains of e.g. neuromotor development, behaviour, cognition and emotional problems [9, 10]. Antipsychotic medication was not introduced until the early fifties [11], thus making it is likely that the majority of the parents who participated at that time were not treated with antipsychotics in the early years of the children’s lives. In other words, they may have been quite severely ill and impaired by their psychotic symptoms in the early years of the children’s lives.

However, much has happened since 1962 - both concerning fundamental genetic understanding, diagnostic procedures, methods for measuring neurocognition and in terms of treatment of the disease. The social understanding in society and the public attitude towards psychiatric patients have changed, although stigma and isolation are still major issues. More insight into the diverse psychopathology, the neurocognitive deficits and the psychosocial development of children who later experience an onset of schizophrenia has emerged. We therefore found it relevant and important to use this knowledge in the design of a new high risk study of about the same size and to start examining these children at an even earlier age. Further, it is relevant to use up-to-date, validated and reliable methods capturing the special aspects of development that are relevant for this group.

It lies outside the scope of this paper to review all existing familial high risk studies, although relevant. For the earliest studies, the so called first generation HR-studies a thorough review [12] reports a generalized tendency to find developmental delays and a variety of problems or difficulties that these children may experience already during middle childhood and adolescence. These include neurointegrative problems, social impairments, early syptomatology, and deficits in attention processing and neuromotor functions. Also the emerging evidence for the influence of family enviroment is underlined. A need for future work to clarify developmental patterns within the same individuals is emphasized. A later review from 2003 is in accordance with these early results [13]. However, in general, the field is characterized by different designs and several shortcomings, e.g. only children with an affected mother, children with an affected 1^st^ degree relative, few or no follow-ups, and widespread age groups sometimes with small number of participants. For example the Rochester Family Study [14], the Swedish High Risk Study [15] and the Emory University Project [16] all included only between 25 and 61 HR subjects. The Helsinki High Risk Study [17] included 204 schizophrenia HR children and 204 controls and performed follow-up after 15 years. The group behind the Boston National Collaborative Perinatal Project HR Study (BNCPP [18]) and the Harvard Adolescent High Risk Study [19] has published several papers recently including follow-ups. The Edinburgh High Risk Study has a slightly different approach since it includes children with 2 or more 1^st^ og 2^nd^ degree relatives and has done quite long follow-ups. Also the Israeli High Risk Study (IHRS [20, 21]) and the Jerusalem Infant Development Study (JIDS) [22] deserve mentioning for contributing to the current knowledge. All the studies are pointing in the same direction supporting the neurodevelopmental hypothesis, but no study has to our knowledge been made with all children having the same age, including genetic material in combination with a thorough estimate of environmental factors on a representative cohort.

More recently, research concerning bipolar disorder has started to look at the same patterns, although it has long been well known that a family history of bipolar disorder is the strongest known risk factor for developing the disorder. For example, it has been found that children with familial risk for developing bipolar disorder may show early signs of vulnerability [23]. This is seen as higher rates of anxiety, sleep and mood disorders in childhood and as an increased risk for developing substance abuse in adolescence. These children also show elevated levels of psychopathology and behavioral problems compared to children of non-bipolar parents [24]. There is evidence that those individuals who later develop bipolar disorder report early signs of illness long before adulthood [25]. As with schizophrenia a staging model has been proposed with four stages from well-being to ill, starting in the early ages of childhood with anxiety and sleep disorder, moving to adjustment problems and subaffective states before major depression, ending up in fullblown bipolar disorder [26]. Researchers in this field emphasize the need of a developmental perspective to understand more about the origin of this severe mental disorder and about possibilities for preventive interventions [27–29].

Several environmental factors in both the prenatal and the perinatal periods as well as through infancy and childhood are associated with the risk of developing schizophrenia later in life. This concerns factors regarding the physical environment, e.g. intrauterine infections, complications during pregnancy and birth, or growing up in an urban district [30, 31]. It is also relevant to study factors that influence the child’s psychological development, such as the psychosocial and emotional environment and the everyday surroundings of the child (e.g. growing up in an institution), the degree of illness severity and chronicity of the ill parent, the emotional climate in the family, and experiences of childhood trauma [13, 32, 33]. Offspring of parents suffering from a severe mental illness such as schizophrenia or bipolar disorder are at a higher risk of growing up under adverse circumstances and experiencing traumatic life events (including the possibility of losing contact with one or both parents), which may result in disturbances in attachment and in normal, early cognitive and emotional development [34]. Only few studies have explored the levels of the parents’ psychopathology and their ability to function as caregivers. The associations between the severity and course of illness of the parent, and the rearing circumstances of the child with neurological, cognitive, behavioural and psychopathological risk markers in early childhood have not been specifically investigated before.

#### Early markers of severe mental disorder

Individuals who later develop schizophrenia, show several characteristics during childhood on a group level. This includes lower IQ, cognitive deficits, delayed neuromotor development, language developmental difficulties, emotional problems and poorer social function in childhood as established in longitudinal high risk studies and birth cohort studies [13, 35–43]. Among the most frequently reported characteristics in children at genetic high risk is poor cognitive and neurological functioning. Due to their stability and the high correlation with the underlying genetic burden, these characteristics may be considered as ‘endophenotypes’ that reflect their specific underlying genetic vulnerability [13, 44, 45]. Cognitive dysfunction, poor affective control, and subtle psychosis-like symptoms (PLIKS) are predictors for later development of psychosis in children at genetic risk for schizophrenia [42, 46]. Also, minor physical anomalies (MPAs) have been shown to be associated with an increased risk of psychosis [47].

For patients with bipolar disorder the literature points out that these patients have more frequently had attention deficits and disruptive disorders, increased rates of misuse in adolescence, as well as increased rates of anxiety disorders before the onset of the disease [48]. From this longitudinal, prospective study with 141 offspring (age 12–21) of families with a proband with BP, the authors conclude that anxiety and externalising diagnoses predict major affective illness in adolescence. The presence of syndromal depression, ADHD, disruptive behavioural disorders, and cyclothymic hypersensitive temperamental traits are found to be risk factors for future development of bipolar disorder, although most subjects exhibiting these traits or states do not develop the disease [25].

## Method

### Settings

We will establish a cohort of 520 7-year-old children from Denmark with different genetic risk profiles of schizophrenia and bipolar disorder in a follow-up design.

### Participants

We will conduct a thorough examination of 520 children aged 7 with either 0, 1 or 2 parents diagnosed with schizophrenia spectrum psychosis, which we define as schizophrenia, delusional disorder or schizoaffective disorder (ICD 10-codes: F20, F22 and F25 or ICD 8-codes: 295, 297, 298.29, 298.39, 298.89, 298.99) or bipolar disorder (defined as ICD 10 code F31 or ICD 8-codes: 296.19, 296.39). All children must be born in Denmark to ensure that full information via register data from both parents is accessible; − this is necessary to limit stratification in the genetic analyses. Analyses combining data from the Danish CPR Register (Civil Registration System [49]) and the Danish Psychiatric Central Research Register [50] show that each year approximately 200 7-year-old children are from families where at least one parent is affected with schizophrenia or schizophrenia spectrum psychosis. The number of children with one parent with bipolar disorder is expected to be similar. Approximately 20–30 7-year-old children have *two* parents diagnosed with either schizophrenia or schizophrenia spectrum psychosis and/or bipolar disorder in Denmark every year. During an inclusion period of approximately three years, we will randomly select the following stratified sample of 520 7-year-old children from all parts of Denmark for examination:at least one parent, either a mother or a father, diagnosed and registered with a schizophrenia spectrum psychosis; *N* = 200.at least one parent, either a mother or a father, diagnosed and registered with bipolar disorder; *N* = 120.neither of the parents being treated or registered in mental health services as in- or outpatients for the above-mentioned diagnoses; *N* = 200.

Group (a), (b), and (c) will be matched on urbanicity, community, gender and exact age of the child. Among the children included in group (a) or (b) 30–40 children are expected to have *two* ill parents, and form a special subgroup within the final cohort. The reasons for including a group of low risk controls are to evaluate gene-environment interactions with a control group and to create Danish norms for some of the outcome measures. Finally, this makes it possible to keep the child’s risk status concealed for the child investigator, thus not introducing bias due to specific expectations towards the child.

#### Age seven

The reason for choosing age 7 is that most children in Denmark have started school at this age, which thus represents an important developmental step for the child. Starting school is characterized by increased demands on the child, cognitive and academic, as well as social and practical. From a neurocognitive perspective this phase of a child’s life is characterized by a very rapid cognitive development, e.g. in the frontal lobes as demonstrated in a metaanalysis [51]. At the same time the early development of the child is not too distant to be recalled for the parent being interviewed.

### Exposures

#### Genetic exposure, polygenic risk scores and family history

The Danish Neonatal Screening Bio-bank is a national bio bank holding dried blood spot-samples from all new-borns since 1981 collected for genetic testing for e. g. phenylketonuria [43, 48–50]. All children in VIA 7 are identified in the Danish Neonatal Screening Bio-bank, their DNA extracted, whole-genome amplified and genotyped on the Illumina PsychChip, which is a whole-genome SNP array developed in collaboration with the Psychiatric Genetics Consortium (PGC) for genome wide association studies (GWAS). The data is processed using the bioinformatics pipeline of PGC. Similarly, DNA from blood samples from their parents is genotyped on the same platform. Polygenic risk scores predict case–control status in GWASs of schizophrenia [52, 53]. Constructed from risk alleles at thousands of genetic loci, the polygenic risk scores configure a simple and robust technique to study at a population level an individual’s genetic risk for polygenic traits, e. g. schizophrenia or bipolar disorder. Here, we will test if polygenic risk score alone and in combination with family history is associated with antecedents of schizophrenia or bipolar disorder and any observed associations of environmental exposures. Furthermore, it is possible to use the DNA from the blood spots and from saliva samples at age seven for genome-wide studies of methylation status at birth compared to age seven using the Infinium HumanMethylation450 BeadChip Kit (Illumina). Thus in VIA 7 we will be able to compare the epigenetic blueprint at birth with status at age seven and at later follow-ups. This may allow us to identify signatures of environmental exposures.

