
### Procedures

Seven Ph.D. students, three clinical assistants, three research nurses and two postdocs are responsible for carrying out the clinical characterisation of the children and the parents. The primary research nurse coordinates administrative issues concerning the contacting of the invited families, registers etc. A letter with a small folder briefly describing the investigation is sent to the child’s address. This is followed up by a phone call from the research nurse a few days later, inviting the family to a meeting to learn more about what the implications of participation are. Both parents are asked for written, informed consent before data collection can start. In case of divorced parents, where both parents have custody of the child, as is most common in Denmark, both parents have to accept the child’s participation.

The genetic study ‘Gene Environment’ is presented as a separate study that is optional for all participants and has its own written consent form. The genotypic information about the children is based on blood samples from the Danish Neonatal Screening Bio-bank and for the parents from whole blood or saliva samples, if consent is given. These will be extracted at the time of the examination of the children. Moreover, we also ask for saliva samples from the children for epigenetic analyses. However, we decided not to ask for fresh blood samples from the 7-year-olds for psychological reasons.

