### Strengths

This study is to our knowledge the first study to include such detailed information about the environment of the child, including the thorough description of the child’s development and symptoms during the first 7 years of life.Our study is unique in that all children in the VIA 7 cohort have nearly the same age (within 12 months). This gives us a very detailed level of information of this exact age group, and also makes all comparisons much more accurate.Further, this population based selection of cases and controls at same age limits the heterogeneity of data and will thus increase power, e.g. with respect to environmental exposures. Data from Danish Registers allow us to invite a more representative sample of all high-risk children, since also parents, who are not actively attending treatment, are invited.Our non-biased sampling of exposures supplemented by detailed interviews will increase the validity of exposures.The very comprehensive mapping of cognition, psychopathology, MPA’s etc. will allow a thorough description of multiple important domains of child development.The interdisciplinary approach with data spanning from genetics and biometry to home environment and attachment measures is unique and allows integrative analyses and multidisciplinary interpretation.Participation rates are very high and drop-out rates are negligible in spite of the time consuming battery.DNA material from the children are collected both at birth and at age seven and will allow us to study epigenetic changes over time and comprehensive genotyping of risk alleles.The identification of biological signatures of exposures in utero as measured at birth is absolutely unique.With a planned follow-up at age 11 we will be the first ever to examine a large sample of HR-children twice before adolescence, and we will be able to describe developmental trajectories in more detail than any other study.

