The RDoC project is at its beginning, aiming to build a database that will change the understanding of psychopathology fundamentally. It has a new perspective on research, cutting across diagnostic categories, a perspective that is both useful and necessary when studying developmental psychopathology and early signs of mental illness [111]. The goals of this high risk study are to our conviction nicely aligned with the RDoC initiative in two fundamental ways: First, we are interested in the continuum of psychotic disorders and their expression. While we are collecting clinical information regarding diagnosis, this will help our data be compared to previous studies using DSM or ICD diagnoses. Nevertheless, we believe that the continuum of psychosis and its risk will be very well explored by our design. Second, the phenotypes we assess, whether behaviour, cognition, and so on, are continuous dimensions relevant to all psychotic disorders. While they were not chosen explicitly using RDoC domains, we are covering in some detail, some of those domains, such as working memory, social cognition, or negative affect and reward systems and thus our data will be informative within an RDoC framework. For example, the domain of negative valence/psychopathology is captured in the study both as categorical data (the diagnoses given on the basis of the K-SADS-PL interview) and as dimensional measures on the CBCL (Child Behavior Checklis [69]) and TRF (Teachers Rating Form [69]). The first gives us dichotomous data (diagnosis/no diagnosis), while the other two are continual scores based on information from both the actual caregiver’s and the actual teacher’s concerning observed behaviour and problems of the child and indicating child psychiatric problems. Further, this will be combined with the ratings of the clinical impression of the child during the clinical testing (TOF; Test Observation Form [74]) and will be followed up upon in VIA 11. In terms of the RDoC domain called ‘cognitive systems’ we have data covering all the subdomains (attention, perception, declarative memory, language behaviour, cognitive control and working memory). All together this approach to psychopathology is much in line with the developmental approach that the RDoC is based on. Further, with the perspective of adding scans and blood tests at the 11-year follow-up will give us information that fits into what RDoC calls ‘cells’, ‘molecules’ and ‘circuits’.

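### Methylation is measured in blood spots at birth and in saliva at age 7, so the average birth-to-7 change cannot be separated from the tissue difference

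*Protocol article*

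**What the plan says.** The subsection on genetic exposure, polygenic risk scores and family history names the source of DNA at each age. The birth material comes from a national bio-bank "holding dried blood spot-samples from all new-borns since 1981". The methylation work would use "DNA from the blood spots and from saliva samples at age seven for genome-wide studies of methylation status", comparing birth with age seven on one array platform. The subsection concludes: "Thus in VIA 7 we will be able to compare the epigenetic blueprint at birth with status at age seven and at later follow-ups". It adds, tentatively, that this may reveal signatures of environmental exposures.

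Procedures confirms the age-7 tissue: "we also ask for saliva samples from the children for epigenetic analyses". It also closes off the alternative: "we decided not to ask for fresh blood samples from the 7-year-olds for psychological reasons". Parents may give whole blood or saliva, but this is described for genotyping and not as a paired blood-saliva methylation sample.

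Strengths says that collecting child DNA at birth and at age seven "will allow us to study epigenetic changes over time". Limitations does not mention the difference in tissue. The RDoC project section speaks of "adding scans and blood tests at the 11-year follow-up" without saying that these would be used for methylation.

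**The concern.** A within-child comparison over time normally removes whatever is constant within the child. Here the tissue is not constant: it changes between the two measurements, in the same direction, for every child. If methylation at a site differs between blood and saliva, for example because the cell mixture differs, that site will show an apparent average change from birth to age 7 even when nothing has changed with age.

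What is at stake is the claim that the study can describe epigenetic change over time in these children. More families would not help, because extra children add precision to a quantity that still mixes two effects.

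**Working it through.** The article gives no sample size, power or threshold for methylation, so there is no figure to reproduce. The question is one of identifiability.

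**Inputs from the article**
- Groups of 200 (schizophrenia risk), 120 (bipolar risk) and 200 (controls), 520 in all (Participants).
- Two time points: birth = blood spot, age 7 = saliva (genetic exposure subsection; Procedures).
- No child blood at age 7 (Procedures).

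**Step 1: the average change.** For one site, let *a* be the true mean change from birth to age 7 and *s* the mean saliva-minus-blood difference. The expected within-child difference is

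E(D) = *a* + *s*.

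In a design matrix with intercept, age, tissue and two group indicators, the age and tissue columns are identical (correlation 1). The matrix has 5 columns and rank 4. Checking estimability, *a* alone is not estimable, *s* alone is not estimable, and *a* + *s* is.

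**Step 2: differences in change between groups.** For groups *g* and *h*,

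E(D_g) − E(D_h) = (*a_g* − *a_h*) + (*s_g* − *s_h*).

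- With a tissue effect common to all groups, *s_g* − *s_h* = 0 and the group-by-age contrast is estimable.
- If the tissue effect may vary by group, the matrix has 9 columns and rank 6, and the group-by-age contrast is no longer estimable.

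The same algebra applies to exposed versus unexposed children.

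**Step 3: comparisons within one tissue.** Comparing groups or exposures within birth blood spots, or within age-7 saliva, involves no tissue difference. This includes signatures of in-utero exposure measured at birth.

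**Step 4: what a tissue shift could do (assumed values only).** Suppose the true age change is 0, the SD of the within-child difference is 0.05 on the methylation proportion scale, and the two-sided threshold is 1e-7 (z about 5.33). The probability that a pure tissue shift is declared a change is about

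Φ( shift / (0.05/√n) − 5.33 ).

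I used n = 520, and n = 0.80 × 520 = 416. The second applies the lower bound from Status (over 80% donating genetic material) to the full cohort. That is an assumption, because uptake of child saliva is not reported.

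| Assumed tissue shift | n = 520 | n = 416 |
|---|---|---|
| 0.005 | 0.001 | 0.0005 |
| 0.01 | 0.22 | 0.11 |
| 0.02 | >0.99 | >0.99 |
| 0.05 | about 1.00 | about 1.00 |

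For the shift of 0.01 at n = 520, 0.05/√520 = 0.00219, 0.01/0.00219 = 4.56, and Φ(4.56 − 5.33) = 0.22. The practical effect runs from negligible to near certain, depending wholly on a shift that the article does not give. At each shift below the ceiling, the larger sample makes the false finding more likely.

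**The case against.** **Methylation is peripheral.** It is absent from the aims, the listed main outcomes and the Statistics section. It is introduced as a possibility and belongs to a separately consented optional study. No main comparison of the three groups depends on it. This stands, and it limits the severity.

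**Exposure effects are not lost.** A reader might infer that the tissue switch makes any exposure-related finding from the two time points uninterpretable. The documents do not support that. Exposure signatures are contrasts between children, and a tissue offset common to all children cancels, as step 2 shows. What is missing is a statement of the assumption that makes it cancel.

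**The size of the blood-saliva difference is not documented.** This also stands. Non-identifiability follows from the design alone, but its practical consequence depends on an unknown quantity, so the table above is only an illustration.

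**Detail may lie elsewhere.** The Gene-Environment study has its own approved protocol, which is not shown. Cell-composition adjustment or a bridging sample could be described there, so their absence here does not show that they are unplanned. However, the article itself fixes both tissues, rules out age-7 blood and asserts the property as a strength. No analysis model can recover the average change from the child samples described without outside information or an assumption that those samples cannot test.

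**Age-11 blood could rescue the claim.** The article mentions blood tests at 11 only as a prospect, does not tie them to methylation and does not mention saliva at 11. They would not separate age from tissue between birth and 7. Even a birth-to-11 comparison would set a dried, banked spot against blood that may be of another sample format.

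**Conclusion.** The point holds for the average within-child change from birth to age 7. With blood spots at birth, saliva at age 7 and no bridging sample described, that change is inseparable from the blood-saliva difference in every child with both samples. The claims in the genetic exposure subsection and in Strengths that change over time can be studied are not supported as written.

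It does not extend further. Group or exposure differences in change remain estimable if the tissue effect, including cell composition, is equal across the groups compared. Comparisons within one tissue are sound on this point. A reader might infer that the epigenetic work as a whole is invalid, or that the main results are threatened; neither follows from the documents.

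The identifiability result needs no effect size, threshold or sample size. Any practical bias rests on one further premise, that methylation differs between blood and saliva at the sites studied, which the article does not state or quantify. Severity is moderate.

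**What to change.** 1. Do not interpret the average birth-to-7 difference as epigenetic change.
2. Compare risk groups and exposures separately within birth blood spots and within age-7 saliva, adjusting for estimated cell composition.
3. If a two-time analysis is kept, interpret only group-by-time or exposure-by-time contrasts, and state the assumption of an equal tissue effect, including cell composition, across the groups compared.
4. Amend the sentence in the genetic exposure subsection and the item in Strengths accordingly, and add the tissue difference to Limitations. If the Gene-Environment protocol contains a bridging sample or a tissue correction, refer to it there.
5. Rest any later claim of change on samples of the same tissue and comparable format, if such samples are collected at follow-up.

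Items 1 to 4 need only wording and analysis choices, with no new samples at age 7. The cost is a weaker claim at age 7. Item 5 depends on follow-up sampling that the article does not yet describe.
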